### Data collection and management

2.9

Data collection in this study ran through the entire process of the three parts of the research, following the principles of standardization and real-time, and data management focused on integrity, accuracy and security. In terms of data collection, a standardized designed Case Report Form (CRF) is uniformly used to record the subjects, baseline information, intervention-related data and detection results of each outcome indicator. Among them, instrument detection data such as fNIRS, surface electromyography and isokinetic muscle strength are exported in real time and marked with detection time points and subject numbers, and manually recorded data have to be recorded promptly after the completion of detection to ensure no information omission. In the data management link, a dual-track storage system of electronic database and paper files is established. Electronic data are entered with encryption software and regularly backed up off-site, and paper CRF forms are filed in special filing cabinets by number. A double entry and review system is implemented, with cross-checking after entry completion. If contradictory data are found, the original detection records are traced in a timely manner for verification and correction. The rules for handling missing data were clarified, and abnormal data have to be marked with reasons and reviewed by the research person in charge. The privacy protection norms of medical research are strictly followed throughout the process. All data are only used for the analysis of this study, the personal information of subjects is anonymized, and private disclosure or transmission is prohibited to ensure that the data is traceable, verifiable, safe and confidential throughout the process.

### Statistical analysis

2.10

Statistical analyses will be performed using MATLAB R2024b. fNIRS preprocessing and calculation of HbO/HbR concentrations, functional connectivity (FC), wavelet amplitude (WA), and graph-theoretical measures will be performed using NirSpark V1.8.9. Normally distributed continuous variables will be expressed as mean ± standard deviation, non-normally distributed variables as median and interquartile range, and categorical variables as frequencies and percentages. Normality will be assessed using the Shapiro–Wilk test. *p* < 0.05 will be considered statistically significant.

Baseline data: Baseline variables will be analyzed according to variable type, data distribution, and the number of groups using the t test, analysis of variance (ANOVA), Mann–Whitney U test, Kruskal-Wallis test, or chi-square test, as appropriate.

fNIRS data: Task-related fNIRS data will be analyzed using the general linear model (GLM) implemented in NirSpark to obtain channel-wise HbO and HbR β coefficients for subsequent group comparisons. To reduce the risk of false-positive findings arising from multiple comparisons, statistical tests of channel-wise activation will be corrected using the false discovery rate (FDR). Functional connectivity (FC), wavelet amplitude (WA), and graph-theoretical measures calculated in NirSpark will be exported for subsequent statistical analysis using linear mixed-effects models (LMM), with Bonferroni correction applied to multiple comparisons.

Biomechanical and clinical data: Repeatedly measured sEMG, muscle tension, pressure pain threshold (PPT), VAS, and ODI outcomes will be analyzed using repeated-measures ANOVA when the data are normally distributed. For non-normally distributed repeated measurements, generalized estimating equations (GEE) will be used in Parts 1 and 3, whereas the Friedman test will be used for the low-pressure, medium-pressure, and high-pressure conditions in Part 2. Bonferroni correction will be applied where multiple comparisons are required.

Regression and correlation analyses: For outcomes showing differences across pressure levels, regression analysis will be further performed to examine how the outcomes change with increasing pressure and to identify the pressure level or range associated with a more favorable response. Linear and polynomial regression models will be compared using adjusted R^2^, Akaike information criterion (AIC), and Bayesian information criterion (BIC), and the better-fitting model will be used for interpretation. In Part 2, correlation analyses will be performed among the biomechanical measures. In Part 3, exploratory correlation analyses will be performed between changes in peripheral measures, including muscle tension and PPT, and changes in fNIRS-derived FC and WA. Pearson correlation analysis will be used to assess linear relationships between normally distributed variables, whereas Spearman rank correlation analysis will be used to assess associations between non-normally distributed variables. False discovery rate (FDR) correction will be applied to correlation analyses involving multiple comparisons.

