#### Randomization and blinding

2.3.2

Randomization is standardized in this study in combination with the design characteristics of the three parts of the experiment: The first part is a case–control observational study. After screening through strict inclusion and exclusion criteria, the case group (patients with lumbar muscle strain) and the control group (healthy people without lumbocrural pain) are selected from the eligible population by simple random sampling (15 cases in each group) to ensure sample representativeness, with no inter-group random allocation involved. The second part is a cross-over design study, in which 24 patients with lumbar muscle strain are divided into 3 groups (8 cases in each group) by complete randomization, receiving three sequences of rolling manipulation intervention with low-medium-high, medium-high-low and high-low-medium pressure, respectively. The third part is an interventional trial involving 69 participants in total. 46 patients with lumbar muscle strain are stratified by age and disease duration and then divided into a case intervention group (rolling manipulation intervention, *n* = 23) and a case control group (health education intervention, *n* = 23) by the random number table method; additionally, 23 healthy controls are selected by simple random sampling.

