Oswestry Disability Index (ODI) (Part 3): The primary clinical outcome is the Oswestry Disability Index (ODI). The main analysis will compare the change in ODI from baseline to immediately after the 6th intervention between the case intervention group and the case control group. We expect a greater reduction in ODI in the case intervention group. ODI will also be assessed after the 1st and 3rd interventions to describe the course of clinical change. It covered 10 dimensions including pain intensity, activities of daily living, walking, sitting and sleeping, with 0–5 points for each dimension. The total score is converted into a percentage (0–100%), with a higher score indicating more severe dysfunction. Data are collected before intervention and immediately after the 1st, 3rd and 6th interventions to evaluate improvements in patients’lumbar function. If no more than 1 item is missing, the value is replaced by the average score of the completed items; if 2 or more items are missing, the data are regarded as invalid.

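### The statistical section does not name the Part 3 primary ODI contrast as the test, states no adjustment for baseline ODI or the randomisation strata, and lets a normality test choose the method

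*Protocol article*

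**What the plan says.** Three sections of the protocol article bear on the Part 3 primary analysis.

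- **Section 2.5.2 (primary outcome measures)** fixes the question: "The main analysis will compare the change in ODI from baseline to immediately after the 6th intervention", case intervention against case control. The intermediate visits have a descriptive role only: "ODI will also be assessed after the 1st and 3rd interventions to describe the course of clinical change". Section 2.8 sizes Part 3 as a two-independent-sample comparison of the same change (difference 10, SD 9, α 0.05, power 0.80).
- **Section 2.3.2 (randomization)** says the 46 patients are "stratified by age and disease duration and then divided into a case intervention group" and a control group.
- **Section 2.10 (statistical analysis)** handles ODI in one sentence with sEMG, muscle tension, pressure pain threshold and VAS: "ODI outcomes will be analyzed using repeated-measures ANOVA when the data are normally distributed". Otherwise, "For non-normally distributed repeated measurements, generalized estimating equations (GEE) will be used in Parts 1 and 3". The switch is governed by "Normality will be assessed using the Shapiro–Wilk test". On multiplicity it adds that "Bonferroni correction will be applied where multiple comparisons are required", without defining the family.

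Section 2.10 does not single ODI out as primary, names no effect or contrast, and mentions no covariate.

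**The concern.** A repeated-measures ANOVA with four ODI assessments yields several tests: a group main effect averaged over all visits including baseline, a 3-df group-by-time test, and individual contrasts. Only the contrast of baseline with the 6th intervention answers the question in section 2.5.2. If the statistical section does not say so, the result that decides Part 3 could be picked after the data are seen.

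The method as stated also treats baseline ODI as one more outcome and leaves out the factors on which allocation was stratified. Both are collected, and using them normally gains precision.

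Finally, with a normality pre-test the data choose the primary method. GEE with an identity link estimates the same mean differences. What changes is the standard error, and the usual sandwich form is too small in samples of this size.

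**Working it through.** **Inputs.** Difference 10, SD 9, α 0.05, 18 per arm before attrition and 23 enrolled (section 2.8); four ODI assessments (section 2.5.2).

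**Assumptions, because the article does not give them.** α is two-sided. SD 9 is the SD of change (the alternative is shown in step 5). Correlation r between visits is 0.3, 0.5 or 0.7 with compound symmetry. The effect grows 0/2/5/10 over the four assessments.

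**1. The plan's own figure.** Two-sided at 80% power, difference 10 and SD 9 need 13 per arm (normal approximation) or 14 (t test; power 0.81). The stated 18 does not reproduce at 80%; at 18 per arm the power is 0.90. That is a separate matter. The comparisons below use 18 per arm as stated.

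**2. The stated contrast as a change-score test.** Noncentrality = 10 / (9 × √(2/18)) = 10/3 = 3.33 on 34 df. Power **0.90** (0.96 at 23 per arm).

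**3. Other tests the same ANOVA offers, at 18 per arm.**
- *Group by time.* SD of change 9 gives 2σ²(1−r) = 81, so σ²(1−r) = 40.5. The effects 0, 2, 5, 10 have mean 4.25 and sum of squared deviations 56.75. λ = (18/2) × 56.75 / 40.5 = 12.61 on 3 and 102 df. Power **0.845**. Simulation over three other growth profiles with a Greenhouse–Geisser correction gave 0.82 to 0.90.
- *Group main effect.* Mean difference 4.25, variance of a patient's mean σ²(1+3r)/4. Power **0.66, 0.41, 0.23** at r = 0.3, 0.5, 0.7.
- *Same contrast with Bonferroni over three post-baseline visits* (α = 0.05/3). Power **0.79**.

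**4. ANCOVA on ODI after the 6th intervention, adjusted for baseline ODI.** σ = 9/√(2(1−r)) and residual SD = σ√(1−r²), so the variance relative to the change score is (1+r)/2.

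| r | Residual SD | Variance ratio | Power, 18 per arm |
|---|---|---|---|
| 0.3 | 7.26 | 0.65 | 0.98 |
| 0.5 | 7.79 | 0.75 | 0.96 |
| 0.7 | 8.30 | 0.85 | 0.94 |

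**5. If SD 9 is instead the SD of a single ODI score.** The change-score SD is 9√(2(1−r)) and the ANCOVA SD is 9√(1−r²). Change-score power is 0.78, 0.90, 0.99 and ANCOVA power 0.92, 0.96, 0.995 at r = 0.3, 0.5, 0.7.

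**6. The GEE route under no effect.** This is a simulation of 20,000 trials with r = 0.5, an uncorrected sandwich variance and a chi-square reference.

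| Test | 18 per arm | 23 per arm |
|---|---|---|
| Contrast after the 6th intervention | about 6.3% | about 6.3% |
| 3-df Wald test | 9–10% | 8–8.5% |

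The nominal level is 5%. Ranges cover repeated simulations.

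**7. The strata.** The article does not say how prognostic age and disease duration are, so no gain is computed for them.

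**The case against.** The strongest reply is that section 2.10 lists methods for five outcomes and that section 2.5.2 has already named the main comparison. This largely stands. A reader might infer that the plan cannot test its own primary question, but the contrast can be taken from a repeated-measures ANOVA or from GEE. What is missing is the statement that it is the test.

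A reader might also infer that Part 3 is underpowered. The documents do not support that. With SD 9 as the SD of change, both the contrast (0.90) and the group-by-time test (0.845) exceed the planned 0.80. The low group-main-effect figures depend on an assumed correlation and effect profile, and no section makes that effect primary. An unadjusted change analysis is valid under randomisation; ANCOVA is simply more efficient.

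Two further inferences depend on choices that section 2.10 does not fix. One is that a patient with a missed visit is dropped: section 2.9 refers to missing-data rules, and complete-case handling would be read only from the method's name. The other is that the GEE route necessarily inflates type I error: no variance estimator or reference distribution is specified, and small-sample corrections exist.

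Covariates may also be set in an analysis plan that is not shown. Against that, section 2.10 does fix a method and a switching rule for ODI, and what it fixes is not tied to section 2.5.2 or to the stratified allocation.

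**Conclusion.** The point holds as a gap between the stated question and the stated method. The primary contrast is clear in section 2.5.2 but is not named as the test in section 2.10. Neither baseline ODI nor the allocation strata appear in the model, and Shapiro–Wilk chooses the primary method.

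Baseline adjustment is worth 15% to 35% of the change-score variance, taking power from 0.90 to between 0.94 and 0.98. This rests on SD 9 being the SD of change and r lying between 0.3 and 0.7. The type I error concern is conditional and modest for the contrast of interest (about 6.3%). It reaches 8–10% only for the 3-df test, in both cases with uncorrected errors. The primary comparison remains valid. The change is worth making because it removes ambiguity over the deciding test and gains precision from data already collected.

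**What to change.** In section 2.10, give the Part 3 ODI analysis its own paragraph and name one primary model, used whatever Shapiro–Wilk shows:

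- either ANCOVA of ODI after the 6th intervention, or a mixed model for ODI after the 1st, 3rd and 6th interventions with arm, visit and arm by visit, an unstructured covariance and Kenward–Roger or Satterthwaite degrees of freedom;
- with baseline ODI, age stratum and disease-duration stratum as covariates in either case;
- with the arm difference after the 6th intervention and its 95% CI as the single primary result, outside any Bonferroni family formed by the descriptive visits.

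If residuals are clearly non-normal, add a permutation or bootstrap analysis as sensitivity and keep the primary model. If GEE is kept anywhere, specify a small-sample variance correction.

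The cost is wording, best settled before unblinding, plus about three degrees of freedom. Going from 34 to 31 df in step 4 of the working changes power by less than 0.002 at each correlation. No new data are needed.

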### Sample size calculation

2.8

Based on the core research objectives and design types of the three parts, this study is overall planned as follows:

The first part is an observational study, with the fNIRS-derived cortical hemodynamic response (HbO/HbR changes) as the primary outcome. Based on repeated measures analysis of variance (effect size *f* = 0.286, α = 0.05, 1−β = 0.8) (30), G*Power 3.1.9.7 calculation showed that 12 cases are needed in each group. Considering a 20% attrition rate, 15 cases are included in both the healthy control group without lumbocrural pain and the lumbar muscle strain case group, with a total of 30 cases.

The second part is a cross-over design. The sample size was estimated based on the median frequency (MF) of the surface electromyographic (sEMG) signals, one of the primary electromyographic outcomes for screening the optimal pressure. Referring to our previous study on rolling manipulation in patients with lumbar muscle strain (13), the within-individual standard deviation of sEMG frequency was 17.09 Hz and the intraclass correlation coefficient was 0.5. Repeated Measures ANOVA combined with Greenhouse–Geisser corrected F test (α = 0.05, 1-β = 0.8) was adopted. PASS 2021 software calculation showed that 17 cases are needed. Considering a 20% attrition rate, 24 patients with lumbar muscle strain are included and randomly divided into 3 group sequences.

The third part took the change in the Oswestry Disability Index (ODI) from baseline to immediately after the 6th intervention as the primary clinical endpoint for the comparison between the case intervention group and the case control group. Based on a two-independent-sample design, in which the expected between-group difference (μ2 − μ1 = 10) and the standard deviation (σ = 9) were derived from a previous study on massage combined with functional exercise for chronic lumbar muscle strain (31), With α = 0.05 and 1 − β = 0.80, the calculation showed that 18 patients were required in each group. Considering a 20% attrition rate, 23 patients with LMS will be enrolled in the case intervention group and 23 in the case control group, resulting in a total of 46 patients with LMS. In addition, 23 healthy controls will be enrolled as a reference group for the fNIRS and biomechanical comparisons. Therefore, Part 3 will include 69 participants in total, comprising 46 patients with LMS and 23 healthy controls.

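### As first-line methods, repeated-measures ANOVA and (in Part 2) the Friedman test discard partial records although 20% attrition is planned; the mixed model already used for fNIRS would keep them

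*Protocol article*

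**What the plan says.** **Method.** Section 2.10 (biomechanical and clinical data) states that repeatedly measured sEMG, muscle tension, PPT, VAS and "ODI outcomes will be analyzed using repeated-measures ANOVA when the data are normally distributed". For non-normal data, "generalized estimating equations (GEE) will be used in Parts 1 and 3, whereas the Friedman test will be used" for the three pressures in Part 2. Normality is judged by the Shapiro-Wilk test. The same section sends functional connectivity, wavelet amplitude and graph measures to a different model class: they are "exported for subsequent statistical analysis using linear mixed-effects models (LMM").

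**Primary outcomes affected.** Under section 2.5.2 these are the sEMG changes across three pressures in Part 2 and ODI in Part 3. The main ODI analysis is to "compare the change in ODI from baseline to immediately after the 6th intervention between the case intervention group and the case control group". The measurement schedule has four visits: "Data are collected before intervention and immediately after the 1st, 3rd and 6th interventions". The 1st- and 3rd-session values serve to describe the course.

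**Missing data.** Section 2.8 allows for 20% attrition in each part; for Part 2, "Considering a 20% attrition rate, 24 patients with lumbar muscle strain are included". The only missing-data rule printed is for ODI items: one missing item is replaced by the mean of the others, and "if 2 or more items are missing, the data are regarded as invalid". Section 2.9 says that missing-data rules were settled but does not give them.

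**The concern.** The method named first for two primary outcomes does not tolerate gaps, in a study that expects one participant in five to leave. A Part 2 patient who finishes two of three pressures contributes nothing under either branch. A Part 3 patient who leaves after session 3 contributes nothing if the data pass the normality test, but contributes the early values if they fail it. The membership of the analysis then depends on a test of distribution shape.

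Two things are at stake: precision, and selection. Part 3 participants know whether they receive manipulation or education (section 2.3.2), so those who leave one arm may differ in early progress from those who leave the other. A completer analysis ignores the early values that would show this.

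**Working it through.** **1. The plan's own numbers.**
- Part 3: 18/0.8 = 22.5, so 23 per arm. Part 2: 17/0.8 = 21.25, so 22; 24 is the next multiple of three. The attrition allowance reproduces.
- Expected completers: 23 × 0.8 = 18.4 per arm against 18; 24 × 0.8 = 19.2 against 17.
- Inputs for 18 per arm: "the expected between-group difference (μ2 − μ1 = 10) and the standard deviation (σ = 9"), α 0.05, power 0.80. n = 2(z₁₋α/₂ + z₁₋β)²σ²/δ² = 2(1.96 + 0.84)² × 81/100 ≈ 12.7, so 13 (14 with the t distribution). The figure of 18 matches two-sided 90% power instead. So 18 completers per arm give power of about 0.90, and 23 give about 0.96. The 17 for Part 2 cannot be checked, because no detectable difference is stated.

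**2. Part 2.** Expected leavers: 24 × 0.2 = 4.8. If half leave after session 1 and half after session 2, the completed sessions discarded are 2.4 × 1 + 2.4 × 2 = 7.2. Standard error of a pressure contrast (total SD = 1, period effects fitted, the document's ICC of 0.5):

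| Analysis | SE | Reduction |
|---|---|---|
| Completers (19.2) | 0.2282 | – |
| All data, leavers split as above | 0.2186 | 4.2% |
| All data, all leave after session 2 | 0.2138 | 6.3% |

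For an assumed ICC of 0.3 to 0.7 the reduction runs from 3.7% to 6.6%.

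**3. Part 3, scattered missing values.** Assume that each post-baseline ODI value is missing independently with probability m.
- Complete on all four visits: 46(1 − m)³ = 39.4 at m = 5%, 33.5 at 10%.
- Baseline and session 6 present: 46(1 − m) = 43.7 and 41.4.
- Approximate variance ratio, four-visit to two-value: 1/(1 − m)² = 1.11 and 1.23.

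Simulation against a likelihood model using all visits (SD 12, correlation 0.7, so SD of change 12√0.6 = 9.3) gives about 10% and 26% extra variance for the four-visit ANOVA. For the two-value change it gives 0% to 3%. Separate runs of the four-visit case varied from 10% to 19% at m = 5% and from 22% to 32% at m = 10%.

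**4. Part 3, dropout before session 6.** Simulation with 23 per arm, true ODI reduction 10 points greater with manipulation, SD of change 9, about 20% dropout, and half the leavers also missing session 3. Where dropout depends on response, the log-odds of leaving rise by 1.2 per SD of poorer change to session 1. There were 800 trials per row; each pair is for visit correlation 0.5 and 0.7.

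| Assumed dropout | Completers | Mixed model |
|---|---|---|
| Random | 10.11, 9.91 | 10.13, 9.92 |
| Poor early responders, both arms | 9.95, 10.05 | 9.97, 10.10 |
| Poor early responders, control only | 9.16, 9.15 | 9.96, 10.05 |
| Poor responders leave control, good responders leave treatment | 8.14, 8.07 | 9.95, 9.87 |

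With random dropout the SD of the estimate falls from 3.09 to 2.96 and from 3.00 to 2.94, that is by 4% and 2%. A further run of the last two patterns gave completers about 9.1 and 7.9, and the mixed model 10.2 to 10.3.

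**The case against.** A reader might infer that all Part 2 and Part 3 results rest on full completers. The document does not support that: non-normal Part 3 data go to GEE, which keeps partial records (though unweighted GEE needs them to be missing completely at random).

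A reader might also infer that a missing session-1 or session-3 ODI form removes a patient from the main test. Section 2.5.2 fixes a contrast needing only baseline and session 6, and section 2.8 sizes it as a two-sample comparison. Section 2.10 does not say that all four visits enter the primary ANOVA. The larger variance figures apply only on that reading.

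The loss of numbers is already budgeted, as step 1 shows. The unprinted missing-data rules might provide for imputation, in which case nobody need be dropped. The bias patterns are assumed, treatment lasts two weeks, and in these scenarios bias shrinks the effect. No loss has been shown for Part 1.

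All of this stands, and it limits the size of the point. It does not remove the point. Both Part 2 branches need complete blocks. Inflating the sample replaces numbers but does not undo selection. The two-value contrast is as exposed to differential dropout as the four-visit one, because it too ignores the interim values that predict leaving.

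**Conclusion.** The point holds in a limited form. In Part 2 both named methods discard partial records. In Part 3 the normal-data branch does, and the GEE branch does not. The cost in precision is modest: roughly 4% to 7% of the standard error in Part 2, and near nil for the ODI contrast as section 2.5.2 defines it. It reaches about 10% to 26% of variance only if all four visits enter the ANOVA with 5% to 10% missing per visit.

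Bias arises only if response-related dropout differs between arms; with the same pattern in both it is about nil. Under the assumed differing patterns, completers give about 8 to 9 against a true 10, and the mixed model about 10. These sizes rest on the assumed correlations, dropout rate and strength of dependence, none of which the article supplies apart from the 20% and the Part 2 ICC. Planned power for ODI is not threatened on the stated inputs. The reason to change is that a better method is already in the plan for other outcomes and costs little.

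**What to change.** In section 2.10, make a linear mixed model on all available values the first-line analysis for sEMG in Part 2 and for ODI, VAS, PPT and muscle tension in Part 3, whatever the normality test shows.
- **Part 3:** arm, time and arm-by-time with an unstructured within-person covariance; the arm difference in change is read at session 6.
- **Part 2:** a participant random effect, so that patients with one or two completed pressures contribute.
- **Both:** state that data collected before withdrawal are included. Section 2.2.3 groups withdrawals with eliminations, and a mixed model recovers nothing from people removed from the data set.
- Keep the completer ANOVA as a sensitivity analysis.

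The cost is wording; the model class is already planned for the fNIRS measures. The downside is reliance on missing-at-random, which cannot be verified but is weaker than what a completer analysis generally needs. Part 1 needs no change on this ground.

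### GEE is the fallback test with only 12–23 participants per group and no small-sample adjustment stated; in its usual form it would be mildly liberal, which one sentence in 2.10 would cure

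*Protocol article*

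**What the plan says.** Section 2.10 sets the rule for the biomechanical and clinical outcomes: "Repeatedly measured sEMG, muscle tension, pressure pain threshold (PPT), VAS, and ODI outcomes will be analyzed using repeated-measures ANOVA when the data are normally distributed". Otherwise, when they are not normally distributed, "generalized estimating equations (GEE) will be used in Parts 1 and 3". The switch is decided by a test: "Normality will be assessed using the Shapiro–Wilk test". The significance threshold is p "< 0.05 will be considered statistically significant", with no sidedness given. The section names no variance estimator, working correlation, small-sample correction or reference distribution for GEE.

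Section 2.8 fixes the group sizes. For Part 1, "12 cases are needed in each group", raised to 15 for attrition. For Part 3, "the calculation showed that 18 patients were required in each group", raised to 23.

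Three further places determine which test is run at which size:
- Section 2.5.2 makes the main Part 3 ODI analysis a single contrast between the two patient groups: the change from baseline to after the 6th intervention.
- Section 2.4.3 and Table 2 give the patients in Part 3 four assessments of ODI, VAS, muscle tension and pressure pain threshold.
- Table 2 marks muscle tension and pressure pain threshold in Part 1 before and after only. Section 2.5.3 is looser and speaks of each time node.

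The fNIRS measures do not use this fallback. Connectivity, wavelet and graph measures are "exported for subsequent statistical analysis using linear mixed-effects models (LMM"), and the task responses use the general linear model.

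**The concern.** Ordinary GEE inference relies on the sandwich variance and on a normal or chi-square reference. Both are large-sample results in the number of independent participants, here 24–30 in Part 1 and 36–46 patients in the Part 3 ODI comparison. At these sizes the sandwich variance is biased low and the reference distribution is too narrow, and both errors push towards false positives. The plan would thus move from repeated-measures ANOVA, whose F reference has finite degrees of freedom, to a large-sample method in a small study.

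If the fallback is triggered, the primary ODI comparison and the secondary Part 1 and Part 3 outcomes could carry p-values somewhat too small and intervals somewhat too narrow. This concerns the standard errors of the fallback itself, not the choice made by the normality test.

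**Working it through.** **Inputs.** From 2.8: 12 and 15 per group (Part 1), 18 and 23 per group (Part 3). From 2.5.2: a 1-df ODI contrast. From 2.4.3 and Table 2: four times in Part 3 (3 df for group by time) and pre/post in Part 1 (1 df). From 2.10: alpha 0.05. Assumptions: two-sided test, complete data, two equal groups, identity link, uncorrected sandwich. The simulations also assume a within-person correlation of 0.5.

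**The plan's own figures.** It states no type I error for GEE, so there is none to reproduce. The attrition step reproduces: 12/0.8 = 15 and 18/0.8 = 22.5, rounded up to 23. The 18 itself does not follow at 80% power from a difference of 10 and SD 9, which give 13 (normal) or 14 (t). That is a separate matter; here 18 only sets n.

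**Exact rate for normal data.** Let S be the pooled covariance of the change scores, on 2n − 2 df. The uncorrected sandwich variance of the group difference is (2n − 2)S/n² = (2/n)S × (n − 1)/n, which is too small by the factor (n − 1)/n. The Wald test with p df therefore rejects when Hotelling's T² exceeds χ²(0.95, p) × (n − 1)/n, where T² × (2n − p − 1)/[p(2n − 2)] follows F(p, 2n − p − 1).

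Example, ODI contrast, n = 18, p = 1: the threshold is 3.841 × 17/18 = 3.628, and P(F(1, 34) > 3.628) = 6.5%. For p = 3: 7.815 × 17/18 = 7.381; 7.381 × 32/(3 × 34) = 2.316; P(F(3, 32) > 2.316) = 9.4%.

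**Skewed data.** Since GEE is used only after normality is rejected, the same test was simulated with lognormal data (log-scale SD 0.6 for moderate skew, 1 for strong skew), 8,000 runs per setting. The Monte Carlo standard error is √(0.06 × 0.94/8000) ≈ 0.27 percentage points.

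| Test | n per group | Normal (exact) | Moderate skew | Strong skew |
|---|---|---|---|---|
| ODI main contrast, 1 df | 18 | 6.5% | 6.2% | 5.6% |
| ODI main contrast, 1 df | 23 | 6.2% | 6.0% | 5.2% |
| Part 1 pre/post, 1 df | 12 | 7.4% | 7.1% | 6.3% |
| Part 1 pre/post, 1 df | 15 | 6.9% | 6.3% | 5.7% |
| Part 3 group by time, 3 df | 18 | 9.4% | 8.9% | 7.9% |
| Part 3 group by time, 3 df | 23 | 8.3% | 7.5% | 6.1% |

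A longer repeat put the lowest ODI cell at 5.3%, within simulation error of 5.2%, so 5.3% is used as the low end. A fitted GEE (exchangeable, robust, moderate skew, 1,000 runs) agreed: 5.9% and 8.4% at 18 per group, 5.7% and 8.4% at 23 (1 df and 3 df), and 7.9% for Part 1 pre/post at 12. If Part 1 used three time nodes, the 2-df test on normal data would give 9.6% at 12 per group and 8.6% at 15.

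**After correction.** In these designs each participant's leverage on the change contrast is 1/n. Kauermann–Carroll divides the variance by (1 − 1/n), which restores the pooled variance; Mancl–DeRouen divides by (1 − 1/n)². With a t reference on the 1-df contrast, simulated rejection over the settings in the table was:
- Mancl–DeRouen: 4.3–4.7% (normal), 3.5–4.5% (moderate skew), 3.0–3.6% (strong skew).
- Kauermann–Carroll type: 4.9–5.3%, 4.4–4.9% and 3.8–4.1%.

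A fitted GEE with bias-reduced covariance (moderate skew, still with the z or chi-square reference) gave 5.4% for Part 1 at 12 per group. In Part 3 (1 df and 3 df) it gave 3.9% and 4.8% at 18 per group, and 5.0% and 5.0% at 23.

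**The case against.** The strongest objection is that the article names GEE and nothing more. Each inflated figure presumes an uncorrected sandwich with a large-sample reference, which the article does not state, and a condensed protocol may leave the covariance estimator to a fuller document. This stands as a condition on the numbers and a reason for low severity. It does not dispose of the point: the article chooses GEE by name for groups this small, and unqualified GEE is ordinarily run in the uncorrected form, which errs in one direction.

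A reader might infer more than the documents support:
- **Error rates up to 12%.** That needs 12 per group and a 3-df test (12.3% for normal data). No part combines them: the four-time schedule belongs to Part 3 with 18–23 per group, and Table 2 gives the Part 1 outcomes before and after only.
- **ODI tested with 12 per group.** ODI is collected only in Part 3.
- **A seriously compromised primary result.** The ODI analysis is a 1-df contrast, for which the excess is at most about 1.5 percentage points, and less with skewed data, the very situation in which GEE is used. The larger figures belong to joint tests that are not the stated main analysis.
- **GEE must be replaced by the linear mixed model already planned for fNIRS measures.** A Gaussian model for data judged non-normal is debatable, and its error rate was not simulated here.

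**Conclusion.** The point holds in a limited, conditional form. If the fallback is triggered and GEE is run without a small-sample correction, it is mildly liberal: about 5.3–6.5% for the primary ODI contrast, about 6–7.4% for Part 1 pre/post outcomes, and about 6–9.5% for joint four-time tests in Part 3. Strong skew gives the lower values and normality the upper ones. The direction is secure for an uncorrected sandwich at these sizes. The exact size depends on the shape of the data, on dropout (complete data were assumed) and on the software settings. Severity is low. If a fuller plan already specifies a correction, citing it settles the matter.

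**What to change.** Keep GEE as the fallback and add one sentence to 2.10: in Parts 1 and 3 it will use a small-sample corrected covariance (Kauermann–Carroll or Mancl–DeRouen, named in advance) with a t reference for single contrasts and an F reference for joint tests. Moving these outcomes to a linear mixed model is optional and not needed to resolve the point.

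The cost is slightly wider intervals. With Kauermann–Carroll and t on 2n − 2 df, the ODI interval at 18 per group widens by √(18/17) × 2.032/1.960 ≈ 1.07, and at 23 per group by √(23/22) × 2.015/1.960 ≈ 1.05. For Part 1 at 12 per group the factor is √(12/11) × 2.074/1.960 ≈ 1.11. Under strong skew the corrected test becomes mildly conservative, at about 3–4%. Of the two, Kauermann–Carroll stays nearer 5% in these simulations. No change to sample size or schedule is needed.
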